### Exploration of AI for radiologists’ training

Dynamic changes in the sensitivity and specificity of intracranial aneurysm diagnosis will be tracked from the first 7 days after the study begins through to the last 7 days before the study ends across all centers.

### Safety evaluation

Participants will not be exposed to the investigational product (AI software) but only their head CTA exams. The interventions in this study will not add additional risks to participants compared to routine head CTA interpretation practice. Therefore, adverse events caused by the investigational product are not applicable in this study.

However, if a patient experiences an unexpected adverse event unrelated to the intervention and requires disclosure of study assignment information, unblinding can be performed by statistician with the admission of the PI. Unexpected adverse events unrelated to the intervention will be evaluated according to the Common Terminology Criteria for Adverse Events [33]. The time of occurrence, expiration, interventions, and treatments will be recorded.

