
### Ethical safety outcomes

Rates of intracranial aneurysms, intracranial arterial stenosis (≥ 50%), occlusion, and intracranial tumors from the final radiology reports will be calculated during the trial and compared with those for the previous 3 months. A reduction in positivity rates of no more than 5% during the trial period will be considered to meet the safety outcome; otherwise, the study will halt to find the reason at the site.

We will further evaluate the false-positive findings that require unnecessary follow-up tests or treatment and extra radiologists’ ruling out time, as well as the false-negative findings that may cause catastrophic consequences.

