In addition, we chose intracranial aneurysms as the target lesion not only because of the challenges of diagnosis but also because of continued uncertainty regarding the optimal management of unruptured intracranial aneurysms (preventive aneurysm repair versus observation) [4]. This paradox would be exacerbated by increasing the detection rate of unruptured aneurysms by the introduction of AI models, especially small aneurysms. It is not clear whether more detected unruptured intracranial aneurysms, assisted by AI technology, would favor patient prognosis, and whether increased detection would increase unnecessary preventive aneurysm repair, or false-positive and small or tiny aneurysms cause patient anxiety and depression in downstream management. Therefore, the target patients are those with mRS ≤ 3 who can participant in questionnaire inquiry and unlikely harboring ruptured aneurysms, to explore the impact of AI on intracranial aneurysms, and highlight the real-world influence of AI on clinical practice, especially in the field of interpretation of medical images.

We plan to enrol 6450 participants in more than 10 provinces across China to represent the influence of AI in clinical practice at a national level. The study is the first prospective double-blinded RCT of AI in radiology and will provide the highest-level evidence for the application of AI systems in clinical settings, not limited to intracranial aneurysms. It is highly expected that the study may set a typical paradigm for AI studies in the radiology field.

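### The safety section rules out AI-caused adverse events and limits grading and unblinding to unrelated events, contradicting the protocol's own account of possible harm

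*Protocol article*

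**What the plan says.** The Safety evaluation section of the protocol article argues that patients themselves are not exposed to the software, only their scans. From this it draws two statements:

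- "The interventions in this study will not add additional risks to participants compared to routine head CTA interpretation practice"
- "adverse events caused by the investigational product are not applicable in this study"

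The adverse-event procedures that follow cover one class of event. Grading is described as: "Unexpected adverse events unrelated to the intervention will be evaluated according to the Common Terminology Criteria for Adverse Events". Unblinding is allowed "if a patient experiences an unexpected adverse event unrelated to the intervention and requires disclosure of study assignment information".

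Other sections treat harm through the report as possible. Ethical safety outcomes says: "We will further evaluate the false-positive findings that require unnecessary follow-up tests or treatment". It adds "the false-negative findings that may cause catastrophic consequences". The Discussion lists as unresolved "whether increased detection would increase unnecessary preventive aneurysm repair, or false-positive and small or tiny aneurysms cause patient anxiety and depression".

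**The concern.** The premise does not carry the conclusion. Under Interventions (Procedures), the AI shows extra suggestions to the junior radiologist, who may change the report. A senior radiologist then releases it, and the patient is managed on that diagnosis. The software therefore reaches the patient through the report. The legend of Fig. 3 accepts that the suggestions shown may be false positives.

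A protocol cannot treat harm from these findings as something to evaluate and also declare it ruled out. At stake is what the safety evaluation can conclude. The trial is meant to support clinical deployment. If its report says that no product-related adverse events occurred, readers will take that as a finding, although the protocol settled it in advance.

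**Working it through.** **1. The sections side by side**

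| Section | Position on harm |
|---|---|
| Safety evaluation | No added risk; product-caused events excluded; grading and unblinding described for unrelated events only |
| Ethical safety outcomes | Consequences of false-positive and false-negative findings to be evaluated |
| Discussion | Effect of AI-assisted detection on repair, anxiety and depression not known |
| Sample size calculation | True-AI assumed 2 points less specific than Sham-AI |
| Secondary outcomes | Treatment complications, DSA yield, rupture, SAH, stroke, mortality, HADS and PHQ-9 compared by arm at 3 and 12 months |

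The first row cannot stand with the next three. The last row shows that harm data are collected, but outside the adverse-event pathway and without a relatedness judgement.

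**2. Checking the plan's specificity figures**

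Inputs from Sample size calculation: specificity 0.90 (Sham-AI) and 0.88 (True-AI), margin 0.05, one-sided alpha 0.025, power 0.80, attrition 5%. The final sample has 5676 patients without aneurysm, or 5676 / 2 = 2838 per arm.

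- Per-arm size: n = (1.960 + 0.842)² × (0.90 × 0.10 + 0.88 × 0.12) / (0.05 − 0.02)² = 7.849 × 0.1956 / 0.0009, giving 1706.
- Total: 2 × 1706 = 3412; 3412 / 0.95 = 3592. The protocol states 3596, so this agrees closely.
- Power with 2838 per arm: Φ(0.03 / √(0.1956 / 2838) − 1.960) = Φ(1.654) = 0.951, as stated.

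The two specificities are therefore the real working assumptions of the plan.

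**3. What they imply for false positives**

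- True-AI: 2838 × 0.12 = 341 patients.
- Sham-AI: 2838 × 0.10 = 284 patients.
- Excess with True-AI: 2838 × 0.02 = 57; after 5% attrition, 57 × 0.95 = 54.
- Excess at the noninferiority margin: 2838 × 0.05 = 142; after attrition, 135.

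The plan thus budgets for about 57 extra patients told of an aneurysm they do not have, and would accept a true loss of specificity approaching 5 points.

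**4. Limits of the figure**

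The safety statement compares with routine reading, and the documents give no specificity for routine reading in this trial. Sham-AI is a proxy. The crossover study described under the investigational product found Sham-AI reading noninferior to reading alone within 5 points, which does not show equality.

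**The case against.** The strongest reply is that the harms are measured where it counts. In a randomised trial, harm is judged by comparing event rates between arms, and Secondary outcomes does this for complications, rupture, SAH, stroke, death and psychological scores, whatever their cause. This stands, and it limits the point.

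A reader might infer that AI-related harms can only be recorded as unrelated, or that the benefit-harm comparison is biased. The documents support neither. No sentence orders a complication after a false-positive report to be classed as unrelated; the printed pathway is silent on it. No section bases the benefit-harm conclusion on a count of related events.

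A reader might also count every false positive and every missed aneurysm as AI harm. That fails too. Junior radiologists read unaided first, and the AI only adds non-overlapping suggestions, so many false positives precede the AI. Misses are planned to be fewer with True-AI: with 774 / 2 = 387 aneurysm patients per arm, 387 × 0.25 = 97 against 387 × 0.35 = 135. Only the excess of about 57 false positives bears on the claim of no added risk.

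Finally, Data collection refers to a Supplementary Appendix for details of the safety evaluation, which is not shown. It may add event categories or a DSA-complication item, so no omission can be asserted. It cannot undo what the Safety evaluation section affirmatively states.

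**Conclusion.** The contradiction is real and should be corrected. Safety evaluation excludes by statement what Ethical safety outcomes and the Discussion set out to examine, and it does not fit the plan's own specificity assumptions, which imply about 57 more false-positive patients with True-AI (about 54 after attrition). That size rests on the planned prevalence and specificities and on Sham-AI as a stand-in for routine reading.

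The consequence is narrower than a loss of safety data, because many of the harms are compared by arm as outcomes. What fails is the adverse-event pathway as printed: it has no place for an event that follows an AI-influenced report. Any statement that no product-related events occurred would be true by definition and could not be offered as evidence. The primary analysis is unaffected.

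**What to change.** 1. Delete from Safety evaluation the statements that the interventions add no risk and that product-caused adverse events do not apply.
2. Reconcile that section with Ethical safety outcomes, Sample size calculation and the Discussion.
3. Let adverse-event grading and the unblinding provision cover events irrespective of relatedness to the intervention.
4. Tabulate by arm: complications of DSA or treatment after an aneurysm report that the reference standard does not confirm; and rupture or SAH in reference-positive patients whose report was negative.

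The cost is small: protocol wording and one extra table, built mainly from data already collected at 3 and 12 months. Secondary outcomes lists DSA use and yield but not DSA complications as such. If the appendix does not already capture them, one item on the follow-up form is needed.

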### Data analysis

#### Sample size calculation

The success of primary analysis requires both the superiority of sensitivity and noninferiority of specificity (with a noninferiority margin of 5% [31]) of the True-AI arm compared to the Sham-AI. Sample size calculations were done with PASS (v21.0.3).

Sample size calculations for superiority of sensitivity: Using a one-sided *α* level of 0.025 and a power of 0.80, we estimated the sensitivity to be 0.65 in the Sham-AI-integrated intracranial aneurysms diagnosis strategy, as opposed to 0.75 in the True-AI-integrated intracranial aneurysms diagnosis strategy according to our previous study ([name], [name], [name], [name], [name], [name], [name], [name], [name], [name], et al: Propose and validation of a placebo control for AI models in intracranial aneurysms detection: a Multi-centre, Multi-reader, Blinded Crossover Study, unpublished). With a 10% increase in sensitivity from Sham-AI to True-AI and accounting for a 5% attrition rate due to that participants withdraw consent [34], we estimated that a sample size of 694 patients with intracranial aneurysms is required to achieve the desired statistical power. Based on our previous experience, assuming a prevalence of intracranial aneurysms in patients undergoing head CTA in the hospital to be 12%, the total sample size needed is 5784, with 5090 patients having no intracranial aneurysms.

Sample size calculations for noninferiority of specificity with a noninferiority margin of 5%: Using a one-sided *α* level of 0.025 and a power of 0.80 and estimating a specificity of 0.90 in the Sham-AI-aided strategy versus 0.88 in the True-AI-aided strategy, along with accounting for a 5% attrition rate, we determined that a sample size of 3596 patients without intracranial aneurysms is needed to achieve the desired statistical power. According to the sample calculations for the superiority of sensitivity, 5090 patients without intracranial aneurysms will be included, providing a power of 0.928.

A sample size iteration was processed from 5784, and the power for coprimary endpoints was 0.742 (0.80*0.928). When the sample size reached 6450, with 774 patients with intracranial aneurysms and 5676 patients without intracranial aneurysms, the power for superiority of sensitivity was determined to be 0.841, and the power for noninferiority of specificity was 0.951. Then, the power for coprimary endpoints was 0.800 (0.841*0.951) (Fig. 4). Therefore, a total sample size of 6450 is finally determined.

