**Methods:**

*Study*
*design*: Prospective, multicenter, double-blinded RCT.

*Settings*: The model was designed for the automatic detection of intracranial aneurysms from original CTA images.

*Participants*: Adult inpatients and outpatients who are scheduled for head CTA scanning.

Randomization groups:

(1) Experimental Group: Head CTA interpreted by radiologists with the assistance of the True-AI-integrated intracranial aneurysm diagnosis strategy (True-AI arm).

(2) Control Group: Head CTA interpreted by radiologists with the assistance of the Sham-AI-integrated intracranial aneurysm diagnosis strategy (Sham-AI arm).

*Randomization*: Block randomization, stratified by center, gender, and age group.

*Primary outcomes:* Coprimary outcomes of superiority in patient-level sensitivity and noninferiority in specificity for the True-AI arm to the Sham-AI arm in intracranial aneurysms.

*Secondary outcomes:* Diagnostic performance for other intracranial lesions, detection rates, workload of CTA interpretation, resource utilization, treatment-related clinical events, aneurysm-related events, quality of life, and cost-effectiveness analysis.

*Blinding:* Study participants and participating radiologists will be blinded to the intervention.

*Sample size*: Based on our pilot study, the patient-level sensitivity is assumed to be 0.65 for the Sham-AI arm and 0.75 for the True-AI arm, with specificities of 0.90 and 0.88, respectively. The prevalence of intracranial aneurysms for patients undergoing head CTA in the hospital is approximately 12%. To establish superiority in sensitivity and noninferiority in specificity with a margin of 5% using a one-sided *α* = 0.025 to ensure that the power of coprimary endpoint testing reached 0.80 and a 5% attrition rate, the sample size was determined to be 6450 in a 1:1 allocation to True-AI or Sham-AI arm.

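### The stated joint power of 0.800 at N = 6450 omits the 5% attrition from its specificity factor; with attrition on both endpoints it is about 0.79.

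*Protocol article*

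**What the plan says.** All places are in the protocol article.

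- **Sample size calculation, sensitivity.** The test is set at a one-sided "level of 0.025 and a power of 0.80". The protocol says "we estimated the sensitivity to be 0.65 in the Sham-AI-integrated intracranial aneurysms diagnosis strategy", "as opposed to 0.75 in the True-AI-integrated intracranial aneurysms diagnosis strategy". With 5% attrition from withdrawal of consent, 694 patients with aneurysm are required. At 12% prevalence this gives a total of 5784, of whom 5090 are free of aneurysm.
- **Sample size calculation, specificity.** The margin is 5 percentage points, with the protocol "estimating a specificity of 0.90 in the Sham-AI-aided strategy versus 0.88 in the True-AI-aided strategy". A 5% attrition allowance is again stated, and 3596 aneurysm-free patients are required. The text adds that "5090 patients without intracranial aneurysms will be included, providing a power of 0.928".
- **Iteration.** At 5784 the joint power is given as 0.80 × 0.928 = 0.742. The total is raised to 6450 (774 with aneurysm, 5676 without). There the sensitivity power is 0.841, "the power for noninferiority of specificity was 0.951", and the product is 0.800. The Fig. 4 legend repeats these final figures.
- **Abstract.** The total of 6450 is presented as chosen "to ensure that the power of coprimary endpoint testing reached 0.80 and a 5% attrition rate".
- **Data analysis plan.** The primary analysis uses the ITT population, from which patients who withdrew consent are excluded. The primary tests are chi-square or Fisher's exact.

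**The concern.** Attrition is defined as withdrawal of consent, and those who withdraw leave the primary analysis set. The loss therefore shrinks both the aneurysm and the aneurysm-free denominators. A joint power that claims to allow for attrition must use the reduced count in both factors. The stated product appears to use it for sensitivity only.

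This product is the sole justification for 6450. The iteration stops at the total where the product reaches 0.800, so there is no slack, and any overstatement in one factor puts the claimed figure out of reach.

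**Working it through.** **Inputs, all from the sample size section.** One-sided α = 0.025 (z = 1.96); sensitivity 0.65 v 0.75; specificity 0.90 v 0.88; margin 0.05; attrition 5%; prevalence 12%; 1:1 allocation. Below, n is the number per arm.

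**Formulas.**

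- Sensitivity, pooled z test: power = Φ{[0.10 − 1.96·√(2·0.70·0.30/n)] / √[(0.65·0.35 + 0.75·0.25)/n]}
- Specificity, noninferiority z test with pooled variance (mean 0.89): power = Φ{[0.03 − 1.96·√(2·0.89·0.11/n)] / √[(0.90·0.10 + 0.88·0.12)/n]}. The 0.03 is the margin of 0.05 less the assumed difference of 0.02.
- Joint power is the product of the two, as in the protocol.

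**Step 1: reproduce the component sizes.**

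- Sensitivity: 80% power needs n = 329; 329/0.95 = 346.3, rounded up to 347; 2 × 347 = 694, as stated.
- Specificity: 80% power needs n = 1708; 1708/0.95 = 1797.9, rounded up to 1798; 2 × 1798 = 3596, as stated.

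Both sizes include the 5% allowance, as the text says.

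**Step 2: find the basis of each stated power.**

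| Endpoint and count | Stated power | Full count | After 5% loss |
|---|---|---|---|
| Sensitivity, 694 | 0.80 | 0.821 | 0.801 |
| Sensitivity, 774 | 0.841 | 0.860 | 0.842 |
| Specificity, 5090 | 0.928 | 0.928 | 0.915 |
| Specificity, 5676 | 0.951 | 0.951 | 0.941 |

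Worked for the final row, full count, n = 2838: (0.03 − 1.96 × 0.008306)/0.008302 = 1.653, Φ = 0.951. After 5% loss, n = 2696.1: (0.03 − 1.96 × 0.008522)/0.008518 = 1.561, Φ = 0.941.

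Worked for sensitivity at 774 after 5% loss, n = 367.65: (0.10 − 1.96 × 0.033799)/0.033597 = 1.005, Φ = 0.842.

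At both steps of the iteration the sensitivity power matches the reduced count and the specificity power matches the full count.

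**Step 3: reproduce the stated product.** Mixed basis: 0.8425 × 0.9508 = 0.801, against the stated 0.800 (0.841 × 0.951).

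**Step 4: put both factors on the stated basis, 5% attrition.**

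- N = 6450: 0.8425 × 0.9408 = 0.793. With the protocol's own 0.841 it is 0.791. Across pooled, unpooled and Farrington-Manning variances the range is 0.791 to 0.795.
- N = 5784: 0.8014 × 0.9153 = 0.734, against 0.742.
- With attrition on neither endpoint, N = 6450 gives 0.860 × 0.951 = 0.818. The stated 0.800 therefore matches neither consistent basis under this test.
- A joint power of 0.80 with attrition on both needs about 6546 (6544 to 6566 by variance method), which is 94 to 116 patients more, or 1.5% to 1.8%.

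**The case against.** **The sensitivity figure may not include attrition.** The pooled z test gives 0.842 after attrition, close to 0.841 but not equal to it. Other tests come equally close at the full 774: 0.842 with a continuity correction and 0.843 with Fisher's exact test, which is one of the tests in the data analysis plan. Fisher's test also gives 0.800 at 694 without attrition. This part stands: the sensitivity power is most consistent with 5% attrition, but that is not proved. The attrition reading remains the likelier one. The text says that 694 includes attrition, and 694 follows exactly from 329/0.95 per arm. The continuity-corrected requirement is 349 per arm (698, or 736 with attrition), which does not match.

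Nor would the alternative rescue the claim. Both factors would then ignore the attrition that the abstract says is covered. Under the continuity-corrected test the product after 5% loss would be 0.822 × 0.941, about 0.77. The specificity factor omits attrition on either reading.

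**The effect is negligible beside the other inputs.** This also stands. Prevalence is only approximate. If it were 11% rather than 12% (an assumption for illustration), the same method gives a joint power of about 0.76 at 6450, a larger change than the one at issue.

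**An adjusted analysis would make up the difference.** A reader might infer this, but the document does not support it. The stated primary tests are chi-square or Fisher's exact, and no figure is given for any gain from adjustment.

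**Conclusion.** The stated joint power is wrong as written. Under the protocol's own assumptions, with 5% attrition on both endpoints, it is about 0.79 (0.793) at 6450 and about 0.73 (0.734) at 5784, against 0.800 and 0.742. The specificity part is firm: both stated powers match the full count to three decimals and neither matches the reduced one. The sensitivity part is the most consistent reading, not a certainty.

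A reader might infer that the trial is underpowered or that 6450 must be raised. The figures do not support that. The shortfall is 0.7 of a percentage point (0.9 at most across the variance methods), and no design decision or analysis turns on it. It is a reporting correction to the figure that fixes the sample size.

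The result assumes the stated sensitivities, specificities and prevalence, attrition that falls equally on patients with and without aneurysm, and the protocol's own rule of multiplying the two powers.

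**What to change.** Keep N = 6450 and restate four figures:

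- specificity power at 5784: 0.915 in place of 0.928;
- specificity power at 6450: 0.941 in place of 0.951;
- joint power at 5784: about 0.73 in place of 0.742;
- joint power at 6450: about 0.79 in place of 0.800.

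Carry these through the sample size text and Fig. 4 with its legend. In the abstract, replace the claim that coprimary power reaches 0.80 with a statement that 6450 gives about 0.79 after 5% attrition. State once that both powers are computed on the count after attrition, and name the test behind each. Do not add a claim that covariate adjustment would recover the difference.

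The cost is editorial: no more patients, and no change to the design or analysis.

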**Fig. 4 Fig4:**
[figure not shown]
Power calculation of sensitivity, specificity, and general power according to sample size iteration. The combined power for the entire trial is 0.800 (0.841*0.951) when the sample is 6450, in which the power for sensitivity and specificity is 0.841 and 0.951, respectively

#### Data collection

Data will be collected in a standard case-report form through a web-based electronic data capture (EDC) system and anonymized for further analysis. The data will include baseline information, medical history, lifestyle habits, life quality evaluation, CTA reports, and AI results. Regular quality monitoring and database checking will be performed at each center to ensure data accuracy. In addition, the AI workstation automatically records the reading time for each case in the background. Details of the safety evaluation are provided in the Supplementary Appendix.

